### Data collection: sample collection and laboratory analysis

All women will have a finger prick sample collected for testing for HIV infection and syphilis on site as point of care tests. Samples for HIV will be tested according to the Zimbabwe National HIV testing algorithm with samples tested in series. The syphilis sample will be tested using *DPP*® *Syphilis Screen* & *Confirm* Assay (Chembio Diagnostic Systems, Inc. New York, USA), a near patient test that tests for both Rapid Plasma Reagin (RPR) and Treponema Pallidum Haemagglutination Assay (TPHA) in a single test in 20 min. The results of HIV and Syphilis rapid tests will be returned to all participants on site. All women will also have two dried blood spot samples (DBS) collected for HIV viral load testing, LAg avidity assay testing (for incorporation into a recent infection testing algorithm) [25], drug resistance testing, ART level testing and PrEP level testing as indicated. The results of viral load tests will be made available to women within 4 weeks of the survey. DBS samples will be shipped to University of Cape Town for ART testing to assess presence of ART in FSW with evidence of recent HIV infection and a viral load < 1000 copies/ml and for Tenofovir-diphosphate (TDF-DP) in HIV-negative women reporting use of PrEP (PrEP adherence is defined as ‘*high*’ if Tenofovir-diphosphate (TDF-DP) ≥ 700 fmol/dDBS punch, ‘*low*’ if < 350 fmol/punch, and medium if 700 < TDF-DP ≤ 350 fmol/punch) [26]. For our primary outcome, medium and low levels (< 700 fmol/punch) will be pooled into one category as ‘low’ (Fig. 2). All laboratory staff undertaking laboratory analyses will be blind to trial arm.

In addition, all participants will be asked to provide a self-administered vaginal swab to be tested for STIs *Neisseria gonorrhoea*, *Chlamydia trachomatis* and *Trichomonas vaginalis*. All vaginal samples will be transported within 48 h at 4 °C. Samples will be tested by the Newlands Clinic using Allplex™ STI Essential Assay Q (Seegene Inc Seoul, Republic of Korea). The results of STI tests will be made available to women through the Sisters clinic within 4 weeks of the survey, and free treatment will be made available and contact tracing of sexual partners offered. All laboratory staff undertaking laboratory analyses will be blind to trial arm.

### Sample size and power considerations

The sample size of the trial was based on pragmatic considerations as well as statistical power. We chose to include 22 clusters and to recruit approximately 200 FSW in each cluster. It was not practically possible to include more than 22 clusters from across the country in the trial, and prior work has suggested that it should be possible to recruit 200 FSW in each included cluster, but in some clusters not more than this. We used restricted randomisation to minimise differences by arm. We used the approach of Hayes and Bennett for cluster randomised trials [27] to consider sample size and power. We estimated that 30% of FSW would meet our primary outcome definition. In a 2016 [10] survey, 22% of FSW were at risk of acquisition/transmission of HIV by a measure that did not include verification of self-reported consistent condom use, while in another 2017 survey 28% of FSW were at risk of acquisition/transmission of HIV using the same definition (PrEP was not available at these sites at the time of the survey). In our previous trial, the coefficient of variation between clusters (*k*) was 0.17 so we estimated sample size using *k* of 0.2 and 0.25. In most scenarios, we estimate 90% power to detect a 30% difference in the proportion of FSW who are at risk of HIV acquisition/transmission between the intervention and control arms (see Appendix Table A5). If *k* is 0.25, we have 78% power to detect a 30% difference and over 99% power to detect a 50% difference.

### Statistical analysis

Our approach is based on our previously published approach to the analysis of data from the SAPPH-IRe trial [10, 28]. One substantive difference between the trials is that in the current AMETHIST trial, we were unable to conduct RDS surveys at baseline in any of the 22 clusters because funding for the AMETHIST intervention and its evaluation were secured separately; the intervention was started prior to research funding being finalised.

### Study profile

We will describe the characteristics of clusters recruited to each arm of the study using available programmatic data. Cluster drop-out is not expected but might occur if political or community acceptance for the research protocol is compromised during the trial duration. We will produce descriptive statistics to assess whether there was balance across the two arms in key socio-demographic and potentially confounding variables at the endline RDS survey to be conducted between July and October 2021.

For each arm of the study at endline, we will describe the range and mean size of the sample recruited through the RDS survey in each site and construct participant recruitment trees. We will describe by arm the range and cluster-mean of the number of women who do not recruit two participants and their understanding of the reasons for this. We will construct a trial profile diagram in line with CONSORT principles but adapted for our specific situation.

### RDS diagnostics

We will conduct recommended RDS diagnostics for each site [29] and report our findings according to STROBE guidelines for the reporting of RDS surveys [30]. As in SAPPH-IRe, the community mobilisation activities might plausibly change the structure of the FSW social networks in the intervention sites. Consequently, the RDS sampling process that runs over these networks might be biased by trial arm. To investigate these potential biases we will (1) compare self-reported network degree in the intervention versus usual care sites, (2) compare homophily/similarity between FSW and their personal networks, and between recruiters/recruitees and (3) examine whether the place of recruitment, relationship between recruiter/recruitee and motivation for recruitment differ between arms and compare time to recruit between arms.

### Analysis principles

Our primary analysis will compare FSW recruited in each community without considering direct contact with the intervention components (i.e. an ‘intention to treat’ approach). Data from individual FSW will be summarised for each cluster, and we will express the intervention effect using a prevalence ratio, prevalence difference and associated 95% confidence intervals.

We will calculate cluster summaries using the RDS-II methodology [31]. For unadjusted analysis, we will fit a linear regression model on the RDS-weighted cluster summaries, with a treatment dummy. We will use the *p*-value and confidence intervals for the coefficient of the treatment dummy.

Adjusted analysis will use the ‘two step’ method of Hayes and Moulton [32]. Age is specified a priori and will be included as a potential confounder that could affect the outcome. We will also adjust for other potential confounders that appear imbalanced by arm between survey participants recruited to the endline RDS surveys. Imbalance will be assessed using ‘eyeballing’ and expert opinion. Decisions about factors to be adjusted for will be made prior to the analysts having access to the complete primary outcome data. We will not adjust for any characteristics that may have been influenced by the intervention. To generate adjusted and RDS-II-weighted analysis, step 1, we fit a logistic regression model for each site with the primary outcome as the dependent variable, age and other variables as independent variables. This model will be used to ‘predict’ outcomes for each woman. The predicted values will be multiplied by the inverse of the degree (RDS-II) to account for the sampling design, normalised for the cluster, and cluster summaries calculated. Step 2, we will divide the cluster summaries used in the unadjusted analysis (accounting for RDS only) by the adjusted cluster summaries from step 1 to generate ‘residuals’. We will calculate the prevalence ratio using the regression model described above with the residuals as the dependent variable. We will calculate the ‘residual’ risk difference (RD) by subtracting the predicted prevalence from the RDS-II weighted observed prevalence in each cluster. We will fit a linear regression model on the residuals to calculate the adjusted RD and 95% confidence intervals.

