### Randomisation

Twenty-two sites have been randomised (1:1) to receive the AMETHIST intervention in addition to standard of care or to continue with the standard of care alone. Randomisation was conducted in January 2019 at a public meeting with key stakeholders, MoHCC, district representatives and representatives of female sex worker community from the 22 sites. It was not possible to blind intervention staff or beneficiaries of services to the intervention allocation.

To minimise baseline imbalance between arms, restricted randomisation was used [22]. Restriction factors included province, number of FSW seen in the Sisters programme in 2017, mean age of first-time attenders, proportion of FSW attending the programme who were aged under 20 years of age, proportion of all attendees aware of HIV status, proportion of all HIV-positive attendees on ART and mean number of visits by attendees. Restricted randomisation resulted in a good balance of restriction factors between treatment arms (see Appendix Table A2). Restricted randomisation generated a list of 705,432 potential combinations from which 999 with the closest balance between arms were selected. Non-investigator attendees were invited to withdraw numbers from a bag to see which one of the 999 combinations was selected.

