Both our trial design and analysis strategy have multiple strengths. AMETHIST is the first cluster randomised trial of a risk differentiated, need-based and targeted intervention for HIV prevention and treatment among female sex workers in Africa. The cluster randomised design facilitates the simultaneous estimation of the intervention impact on both HIV-negative and positive women. The research participants contributing to primary endpoint analysis will be recruited through RDS surveys within trial clusters, as in our previous ‘SAPPH-IRe’ trial. RDS reduces sampling bias and improves representativeness of ‘hard-to-reach’ populations by limiting the number of referrals any one respondent can have creating ‘deep’ rather than ‘wide’ sample networks [31]. We have outlined our RDS implementation in advance, described potential biases related to the use of RDS design in practice, attempted to collect information vital to signal whether potential biases exist, and planned sensitivity analyses to quantify their impacts on our findings.

Our design has also limitations: a longer trial would have been preferred. To minimise contamination between FSW communities/spill-over effect, we used 22 clusters, which might compromise the power of the study. However, our study is larger than previous clustered randomised trials of similar interventions in Africa [10]. We also sought to strengthen power by using restricted randomisation based on key characteristics of FSWs to maximise the chance of baseline balance.

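### Allocation was tightly restricted to gain power, but the stated analysis ignores the restriction and picks covariates by apparent endline imbalance. If the restriction factors are prognostic, intervals are too wide and the test is conservative

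*Protocol article*

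**What the plan says.** Four statements in the protocol article bear on this.

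- **Randomisation.** "Restricted randomisation generated a list of 705,432 potential combinations from which 999 with the closest balance between arms were selected". The factors come from the existing programme: "Restriction factors included province, number of FSW seen in the Sisters programme in 2017, mean age of first-time attenders". The list continues with the proportion aged under 20, the proportion aware of their HIV status, ART coverage among HIV-positive attendees, and mean visits, which makes seven. Good balance on them is reported.
- **Discussion.** The purpose is explicit: "We also sought to strengthen power by using restricted randomisation based on key characteristics of FSWs to maximise the chance of baseline balance".
- **Analysis principles, test.** The unadjusted analysis is a linear regression of RDS-weighted cluster summaries on a treatment dummy, using that coefficient's p-value and interval. The adjusted analysis is a two-step method. Step 1 is a logistic model fitted in each site, and step 2 applies the same regression to the residuals.
- **Analysis principles, covariates.** Age is fixed in advance. For the rest, "We will also adjust for other potential confounders that appear imbalanced by arm between survey participants recruited to the endline RDS surveys", judged by eye and by expert opinion. There are two safeguards. Characteristics that the intervention may have influenced are excluded, and "Decisions about factors to be adjusted for will be made prior to the analysts having access to the complete primary outcome data".

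No restriction factor is named as a covariate, and no test uses the list of 999 allocations.

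**The concern.** A treatment-dummy regression judges the observed difference as if any split of the towns could have occurred, whereas only 0.14% of splits could. If the balanced factors predict the outcome, the restriction makes the effect estimate less variable. The standard error is still computed from the full spread of clusters within arms, so it does not register this gain. The interval is then wider than it needs to be, and the test rejects too rarely under the null.

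The covariate rule does not repair this. It looks for variables that differ between arms at endline, and the restriction factors were chosen not to differ. There was no baseline RDS survey (Statistical analysis), so these 2017 programme values are the only pre-randomisation cluster data that the article describes.

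A smaller issue is the word *complete* in the lock on covariate choice. Judging imbalance needs endline data labelled by arm. The questionnaire covers condom use, and HIV results are available on site. As worded, the lock would still permit covariates to be chosen with part of the outcome visible.

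**Working it through.** **Inputs.** There are 22 clusters, 11 per arm (Randomisation). Sample size and power considerations gives m = 200 per cluster, p0 = 0.30, a 30% relative reduction (p1 = 0.21) and k = 0.20 or 0.25. *Assumptions:* two-sided alpha of 0.05, because the section states none, and R², the share of between-cluster variance that the restriction factors explain, varied from 0 to 0.75 because the documents do not give it.

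**1. The plan's own power.** Hayes–Bennett with c = 11:

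- Within-cluster part: 0.30×0.70/200 + 0.21×0.79/200 = 0.00188.
- Between-cluster part at k = 0.25: 0.0625×(0.09 + 0.0441) = 0.00838.
- Sum V = 0.01026.
- z = √(10×0.09²/0.01026) − 1.96 = 0.85, so power is 80.2%.

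The stated figure is 78%. A design-effect version (ICC = 0.0625×0.30/0.70 = 0.0268, design effect 6.33, about 348 effective women per arm) gives 77.8%, and Hayes–Bennett with p0 between 0.24 and 0.28 gives 77.8 to 79.5%. At k = 0.20 the result is 91.7% (stated 90% in most scenarios), and for a 50% reduction it is 99.9% (stated over 99%). The stated power therefore stands, and it takes no visible credit for restriction.

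**2. Tightness.** C(22,11) = 705,432, so the list is every possible split, and 999/705,432 = 0.14%.

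**3. Closed-form approximation.** With near-exact balance, the true variance falls to 0.00188 + (1 − R²)×0.00838, while the dummy-only standard error still estimates 0.01026. The ratio of true SD to reported SE is the square root of the quotient, and the test behaves as if its critical value (2.086 on 20 df) were divided by that ratio.

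| R² | True SD / reported SE | Type I error |
|---|---|---|
| 0.25 | 0.89 | 3.0% |
| 0.50 | 0.77 | 1.3% |
| 0.75 | 0.62 | 0.3% |

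**4. Simulation.** All 705,432 splits were enumerated and the 999 best balanced kept, using six simulated continuous factors plus an assumed eight-level province, with 7,500 to 10,000 trials per cell. The SD ratios came out at 0.90, 0.78 and 0.63, in line with step 3.

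| R² | 0 | 0.25 | 0.50 | 0.75 |
|---|---|---|---|---|
| Planned test, type I error | 4.5% | 2.9% | 1.4% | 0.2% |
| Planned test, power | 80% | 82% | 84% | 87% |
| Same test, unrestricted randomisation, power | 80% | 80% | 79% | 79% |
| Adjusted for the six factors, power | 77% | 86% | 94% | 99% |
| Permutation over the 999, power | 75% | 83% | 90% | 96% |
| Adjusted / planned interval width | 1.04 | 0.91 | 0.78 | 0.61 |

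Type I error was 4.4 to 5.3% with adjustment and 3.9 to 4.7% with permutation. A second run with six simulated factors at R² = 0 / 0.25 / 0.50 gave:

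- planned test: type I error 4.7 / 3.2 / 0.9%, power 81 / 83 / 85%;
- permutation: power 78 / 85 / 93%;
- adjustment for all six factors: power 78 / 87 / 94%.

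The power forgone is thus about 2 to 4 points at R² = 0.25 (1 point in the lowest comparison) and 6 to 10 at R² = 0.50.

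**5. Smaller effect.** For a 15% reduction at R² = 0.50, power is 20% as planned, 26% under unrestricted randomisation, 34% with permutation and 39% with adjustment.

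**6. Where the factors can enter.** They are constant within a town, so they cannot enter a logistic model fitted in each site. Such a model also has its own intercept, so its predictions already average to that site's observed prevalence. Residuals built from them have lost the between-site variation that the restriction factors would explain.

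RDS weighting, the two-step residual analysis and the unknown endline covariates were not simulated.

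**The case against.** The strongest reply is that everything depends on R². The factors describe 2017 programme attenders, whereas the outcome comes from RDS samples in late 2021. PrEP use and verified condom use, both central to the composite, are not among them. The Discussion says that about twice as many of the women who could benefit are HIV-negative as HIV-positive, so ART coverage may predict little. This stands, and the higher R² columns may be optimistic. The Discussion nevertheless expects the factors to strengthen power, which they do only if they are prognostic.

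A reader might infer that the restriction's power is wholly lost. It is not: at the design effect the planned test has 82 to 87% power when R² is 0.25 or more, against about 80% unrestricted. Only for smaller effects can it fall below unrestricted randomisation. A reader might also infer a false-positive risk, but the simulated error goes the other way.

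A reader might infer that the plan adjusts for consequences of treatment, or that analysts will see outcomes by arm. The first is expressly barred. The second rests on one word, and no section says that it will happen.

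Checking endline balance also has a purpose. Participants are sampled after randomisation, and the RDS diagnostics section recognises that sampling could differ by arm. Age overlaps two restriction factors. Finally, a permutation test or a covariate list may sit in the analysis plan, which is not shown. That limits the point to the method and selection rule that the article does state.

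**Conclusion.** The point holds in conditional form. The stated inference does not use the restriction, and the stated covariate rule tends to leave the restriction factors out. That sits badly with the reason given for restricting. If the factors explain a quarter to a half of between-cluster variance, type I error is about 3% to 1%, the SD of the estimate is about 0.9 to 0.8 of its reported SE, and the power forgone is that in step 4. If they explain nothing, nothing is lost.

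These sizes rest on the assumed R², on k = 0.25 and on the treatment-dummy test, and they cannot be carried over to the two-step analysis. The documents do not support saying that the intervals are certainly too wide or that the 78% is wrong. This should be changed because it is cheap and no further clusters are available. It does not threaten the validity of a positive result.

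**What to change.** **Use the restriction.** Do one or both of the following.

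- Report a randomisation-test p-value for the primary comparison over the retained 999 allocations.
- Pre-specify a small set of restriction factors, at their 2017 values, as cluster-level covariates. Enter them in the regression on the RDS-weighted cluster summaries, or in a step-1 model pooled over sites without the treatment term. They should not be added to residuals from a step 1 fitted per site.

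The choice of factors matters. In the second run, adjusting for two factors that were not the prognostic ones gave 84 / 88% power at R² = 0.25 / 0.50, little above the planned 83 / 85%. The randomisation test does not require that choice.

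**Fix the covariates.** Replace selection by apparent imbalance with age plus a short named list of prognostic variables that the intervention cannot change, and keep the existing exclusion of characteristics it may have influenced. Close the list before any component of the primary outcome is seen by arm, which means deleting the word *complete* from the lock. Endline balance can still be reported descriptively.

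**Cost.** Wording only, since the 2017 values were used in the restriction. If the factors prove uninformative, adjustment costs about 1 point of power with two factors (80 to 79% in a smaller simulation) and about 3 with six. The randomisation test costs about 3 to 5.

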### Data collection: questionnaires

Questionnaire data will be collected through self-administration directly onto tablet computers using an audio computer assisted survey instrument (ACASI) in part to minimise reporting bias. Trained research assistants will assist each FSW to log-in correctly and understand the use of the ACASI. The questionnaire will include questions on demographics, sex work, sexual behaviour and condom use, HIV testing history, ART use (including specific drug regimen), stigma, experience of violence, quality of life, mental health, substance use, general health, relationships with other sex workers and use of sexual and reproductive health services. We will collect data to determine personal network size for RDS adjustment: we will ask how many females sex workers the participant knows who are aged over 18, live at the site, who she has seen in the last month and who she would consider recruiting to the study. In addition, we will collect information from consenting women to allow us to link questionnaire data to Sisters programme data.

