Another challenge for our trial design has been in deciding on the most appropriate primary endpoint and how this will be measured. We have proposed a composite endpoint including data on four domains that together reflect the risk of a woman (either HIV positive or negative) being involved in HIV transmission/acquisition. The use of this composite endpoint poses both conceptual and methodological challenges. Composite endpoints are commonly used in clinical trials, including in HIV [38], with the most common reason being that this can increase statistical power. However, difficulties in interpretation are recognised. The multiple outcomes included within a composite endpoint may differ in their importance to clients and providers, may differ in their absolute frequency and may experience different risk reductions as a result of the intervention, and all of these effects influence interpretation [39]. While we do not currently have available population level data among FSW data on the outcome as we will measure it in the trial, we do have similar data from previous RDS surveys, when either 22.0% [10] (no drug levels or verification of reported condom use) or 28.4% [7] (no drug levels but STI test results available) of FSW were positive for our primary outcome, which the intervention seeks to reduce. We anticipate the prevalence of the actual outcome will be higher if validation of self-reports of PrEP and condom use are included. In both scenarios, approximately twice as many women who could be beneficially affected by the intervention are HIV-negative than are HIV positive likely reflecting the stage of the epidemic in Zimbabwe where although there have been considerable gains in terms of treatment coverage, the rate of new infections has remained relatively static [40]. Optimising coverage and continuation of PrEP in AMETHIST sites has the potential to impact our primary outcome.

The key methodological challenge relates to the validity of self-reported data on sexual activity, condom use and uptake/adherence to medications. Our approach assumes that the likelihood that people will report *not* using PreP and/or *not* using condoms when they actually are doing so is low, and so we assign such people as at risk of HIV transmission on the basis of their self-reports. However, for those who report these protective behaviours, our approach is to collect additional information for these individuals to be classified as *not at risk.*

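### The rule for fixing adjustment factors bars sight of only the 'complete' primary outcome, so part of the outcome may be seen by arm before the factors are chosen

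*Protocol article*

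**What the plan says.** All of the adjustment rules are in the Protocol article under Analysis principles. Age is named in advance. For the rest, "We will also adjust for other potential confounders that appear imbalanced by arm between survey participants recruited to the endline RDS surveys". The method of judging is also given: "Imbalance will be assessed using ‘eyeballing’ and expert opinion". Two limits follow. One concerns timing: "Decisions about factors to be adjusted for will be made prior to the analysts having access to the complete primary outcome data". The other concerns which variables are allowed: "We will not adjust for any characteristics that may have been influenced by the intervention".

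The section Statistical analysis explains why endline data are used: "we were unable to conduct RDS surveys at baseline in any of the 22 clusters". The data sources are described under the data collection headings. On the interview: "The questionnaire will include questions on demographics, sex work, sexual behaviour and condom use, HIV testing history, ART use". On HIV status: "All women will have a finger prick sample collected for testing for HIV infection and syphilis on site as point of care tests", with the result returned to the participant on site.

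The Primary endpoint section and the Discussion treat self-reports asymmetrically. A report of protective behaviour must be backed by biological evidence. A report of not using PrEP or condoms is accepted as it stands: "we assign such people as at risk of HIV transmission on the basis of their self-reports".

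**The concern.** When covariates are chosen by inspection and not listed in advance, the main protection against a convenient choice is that the people choosing cannot see the outcome. Here the protection is worded so that it is met as long as some piece of the outcome is still outstanding. Analysts could hold self-reported condom use, self-reported PrEP use and HIV status by arm, choose the adjustment set, and still have followed the plan.

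This matters because the Abstract places the adjusted two-step estimate within the primary analysis, and there are only 22 clusters. If part of the result is visible, it could influence which of several borderline imbalances is thought worth adjusting for. Even if that did not happen, the trial could not show from this rule that the choice was made blind to outcome.

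**Working it through.** The article gives no figure for the share of the outcome available before laboratory results, so there is none to reproduce. The stated power figures do not depend on this point.

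**Step 1: who can be classified from the interview and the on-site HIV test alone.** From the Primary endpoint section:

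- HIV-positive: a viral load is needed for the classification, so status is not final early.
- HIV-negative, reports no condomless sex: Y-chromosome and gonorrhoea results are needed, so status is not final early.
- HIV-negative, reports condomless sex and current PrEP: a tenofovir-diphosphate level is needed, so status is not final early.
- HIV-negative, reports condomless sex and no PrEP: at risk, with nothing further needed. Status is final early.

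Only the last group is fixed early, and all of its members are outcome events.

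**Step 2: inputs for its size.**

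- Expected outcome prevalence: 30% (Sample size and power considerations).
- Earlier at-risk prevalence: 22.0% with neither drug levels nor verified condom use, and 28.4% with no drug levels but with STI results (Discussion).
- About twice as many HIV-negative as HIV-positive women among those who could benefit (Discussion), read here as two-thirds of at-risk women being HIV-negative.

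**Step 3: share of all women, and of expected at-risk women.** Formula: share of all women a = (2/3) × earlier prevalence; share of at-risk women = a / 30%.

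- 22.0% survey: (2/3) × 22.0% = 14.7% of all women; 14.7 / 30 = 49% of at-risk women.
- 28.4% survey: (2/3) × 28.4% = 18.9% of all women; 18.9 / 30 = 63% of at-risk women. This is an upper bound, because some of those women may have been classed at risk through STI results and not through the interview.

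**Step 4: allowance for PrEP.** The sample size section says PrEP was not available at the surveyed sites. It is available at all 22 trial sites, and a woman who reports PrEP drops out of the early-classified group. The article gives no figure for PrEP reporting, so I assume that a fraction u of the group, from 10% to 40%, now reports it. Each share is multiplied by (1 − u).

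- 22.0% survey: 48.9% × 0.9 = 44%, down to 48.9% × 0.6 = 29% of at-risk women. As a share of all women: 14.7% × 0.9 = 13.2%, down to 14.7% × 0.6 = 8.8%.
- 28.4% survey: 63.1% × 0.9 = 57%, down to 63.1% × 0.6 = 38% of at-risk women. As a share of all women: 18.9% × 0.9 = 17.0%, down to 18.9% × 0.6 = 11.3%.

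**Step 5: how informative the early part is.** Every early-classified woman is also a final case. The individual-level correlation between the early flag (prevalence a) and the final outcome (prevalence T = 0.30) is therefore √[a(1 − T) / (T(1 − a))].

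- a = 0.147: √[(0.147 × 0.70) / (0.30 × 0.853)] = 0.63.
- a = 0.189: √[(0.189 × 0.70) / (0.30 × 0.811)] = 0.74.
- a = 0.088 (low end of Step 4): √[(0.088 × 0.70) / (0.30 × 0.912)] = 0.47.

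This reflects individual sampling only and ignores between-cluster variation and RDS weights. It shows that the early part carries real information about the outcome. It does not measure bias in the adjusted estimate.

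**The case against.** The strongest reply is that the article never says analysts will receive these items early. 'Complete' may simply mean the assembled four-domain composite, and the details of data release normally sit in an analysis or data-management plan that is not shown here. A reader might infer that half of the outcome is already known to the analysts when they choose. The documents do not support that. The data exist, but access is permitted and not stated. Nor does 'half of the outcome' fit: half refers to expected at-risk women, and final status is fixed early for only about 15–19% of all women. The percentages also divide earlier surveys' prevalences by a planning value, which mixes populations and definitions.

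A reader might also infer that the HIV test supplies covariates. No section says so; HIV status is an outcome domain. The Primary endpoint section in fact calls it a laboratory test at endline, whereas the laboratory section describes an on-site test with the result returned there.

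The remaining limits are real. The selection criterion is covariate imbalance and not association with outcome. Factors the intervention may have influenced are excluded. The unadjusted analysis cannot be affected. No calculation shows that the choice of covariates would move the estimate or the error rate materially.

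All of this narrows the point without removing it. The article does state a timing rule, so this is not a detail merely left to another document, and the rule as stated is looser than its purpose requires. The exclusion of intervention-influenced factors limits which variables may be used; it does not stop partial outcome results from guiding the choice among those that remain.

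**Conclusion.** The point holds as a weakness in wording with a practical consequence: the rule permits arm-level sight of part of the primary outcome before discretionary covariates are fixed. The part concerned is roughly 15–19% of all women, or 49% of expected at-risk women on the 22.0% survey, with 63% as an upper bound from the 28.4% survey. If 10–40% of the group reports PrEP, it is roughly 29–57% of at-risk women (9–17% of all women). These figures rest on the 30% planning prevalence, the two-to-one split by HIV status, the relevance of the earlier surveys, and the assumed PrEP reporting.

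Whether analysts would in fact look, and what it would do to bias or error rate, is not established. The adjusted estimate is the only one exposed. This is a worthwhile and cheap improvement, not a flaw that undermines the trial.

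**What to change.** Under Analysis principles, replace the reference to the complete primary outcome data with: *any component of the primary outcome by arm (HIV status, self-reported condom and PrEP use, viral load, drug level, gonorrhoea, Y-chromosome)*. Have the imbalance review done on a file that holds arm and candidate covariates but none of those fields, and date the covariate list before the outcome fields are released.

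The cost is one sentence and one extra data-release step. No additional data are needed, and the sample size and power are unchanged.
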